## Abstract

**Background:**

Many health care practitioners use a variety of hands-on treatments to improve symptoms and disablement in patients with musculoskeletal pathology.

Research to date indirectly suggests a potentially broad effect of manual therapy on the neuromotor processing of functional behavior within the supraspinal central nervous system (CNS) in a manner that may be independent of modification at the level of local spinal circuits. However, the effect of treatment speed, as well as the specific mechanism and locus of CNS changes, remain unclear.

**Methods/Design:**

We developed a placebo-controlled, randomized study to test the hypothesis that manual therapy procedures directed to the talocrural joint in individuals with post-acute ankle sprain induce a change in corticospinal excitability that is relevant to improve the performance of lower extremity functional behavior.

**Discussion:**

This study is designed to identify potential neuromotor changes associated with manual therapy procedures directed to the appendicular skeleton, compare the relative effect of treatment speed on potential neuromotor effects of manual therapy procedures, and determine the behavioral relevance of potential neuromotor effects of manual therapy procedures.

**Trial Registration:**

identifier NCT00847769.

## Background

Many health care practitioners use a variety of hands-on treatments to improve symptoms and disablement in patients with musculoskeletal pathology. Often, these manual procedures purport to target specific musculoskeletal structures, such as joints, muscles, or fascia. Procedures that historically have been relevant to joint structures may be placed on a continuum of speed and amplitude. Mounting scientific evidence supports statistically significant and clinically important benefits of manual therapy in subgroups of patients with various forms of musculoskeletal disablement affecting the axial region [1-3] and appendicular region. [4-9] However, studies related to the mechanisms of manual therapy interventions have lagged behind the literature documenting their clinical effects. An improved understanding of the mechanism of clinical improvement with various speeds and amplitudes of manual therapy will lead to the optimization of patient selection for manual therapy procedures. In turn, improved patient selection will optimize efficiency, quality, and cost of health care for patients with musculoskeletal disablement.

Various central and spinal sensorimotor mechanisms of manual therapy procedures recently have been investigated. Inhibition of the Hoffman reflex following spinal manipulation and increased lower extremity muscle strength have been observed following manual therapy directed to the lumbopelvic region in several studies. [10-14] Manual therapy procedures may facilitate descending GABAergic inputs to local spinal circuits that cause the observed H-reflex depression, suggesting a broader effect on the central nervous system (CNS).[15] However, relatively few studies to date have looked into short-term neuroplastic changes in CNS neuromotor processing to manual therapy procedures. To that extent, Dishman and colleagues[16] identified a short-term increase in motor evoked potential amplitude for the lumbar paraspinals in healthy volunteers using single-pulse transcranial magnetic stimulation (TMS) directed to contralateral motor cortex. Haavik-Taylor and Murphy[17] also documented a significant muscle-specific pattern of effects of cervical spine manipulation on short interval intracortical facilitation, short interval intracortical inhibition, and cortical silent period of abductor pollicis brevis and extensor indicis without significant change in F wave in asymptomatic individuals with a history of recurrent neck pain.

Taken together, these results suggest a potentially broad effect of manual therapy on the neuromotor processing of functional behavior within the supraspinal CNS in a manner that may be independent of modification at the level of local spinal circuits. However, several important limitations of existing studies continue to constrain our collective understanding of the CNS changes associated with the clinical effects of manual therapy in patients with musculoskeletal disablement. The use of non-disabled volunteers in the majority of existing research to date may provide limited information regarding the specific effects of mobilization and manipulation in patients with disablement due to pain and weakness. The use of spinal manual therapy as a subject of study potentially jeopardizes the specificity of conclusions that can be drawn, since spinal manipulation is poorly localized even in skilled and experienced practitioners.[18] The absence in the literature to date of behavioral measures to document potential changes in physical performance as a result of manual therapy procedures means the functional relevance of observed CNS neuroplasticity associated with cervical and lumbar manipulation also remains unclear. Also, the effect of procedure speed on CNS neuroplasticity has yet to be examined. A comparison of procedures characterized by a high velocity-low amplitude (HVLA) application of iatrogenic force with procedures that involve a slower, variable-amplitude application of iatrogenic force would be relevant, because they are among the most common clinical procedures in manual therapy.

One promising research design for determining the underlying neural mechanism associated with manual therapy involves the talocrural joint. There are a number of advantages for using the talocrural joint as an experimental preparation for studying the neurophysiological effects of manual therapy procedures. These include (i) the relatively large size of the talocrural joint, (ii) the relatively large size of the muscle groups crossing this joint, and (iii) the talocrural joint is subject to a prevalent injury that may be identified on the basis of a simple history and clinical examination. The large size of the talocrural joint suggests manual therapy procedures may be more specifically directed to this region than a smaller joint of the spine. The relatively large size of the muscles crossing the talocrural joint provide for easily reproducible recording sites for transcranial magnetic stimulation with electromyographic recording (TMS/EMG). Valid and reliable behavioral measurements for talocrural joint range of motion and lower extremity functional behavior exist. These measurements will allow for empirical examination of the relationship between short-term CNS neuroplasticity and the changes in functional behavior that have been elucidated by clinical studies.

The purpose of this paper is to describe methodology for using the talocrural joint as an experimental preparation to study the neuroplastic CNS changes associated with mobilization and manipulation. The specific aims of this study are to (1) determine the same-day test-retest reliability of TMS/EMG in individuals with post-acute ankle sprains, (2) quantify corticospinal excitability in individuals with post-acute ankle sprains receiving HVLA ankle manual therapy, slow ankle manual therapy, and control intervention; and (3) relate changes in corticospinal excitability in individuals with post-acute ankle sprains receiving HVLA ankle manual therapy, slow ankle manual therapy, and control intervention to short-term changes in lower extremity function.

## Methods/Design

### Subjects

Subjects with post-acute ankle sprains (n = 27) will be enrolled into the study. Inclusion criteria include (i) subject age between 18–60 years, (ii) onset of ankle sprain at least 2 weeks prior to enrollment, (iii) Foot and Ankle Ability Measure Activity of Daily Living subscale score >20%, and (iv) ankle dorsiflexion range of motion limitation greater than 2 standard deviations from published values.[19] Exclusion criteria include (i) assisted ambulation (eg, cane or crutches); (ii) inability to bear weight through the affected extremity immediately after injury; (iii) tenderness to palpation of the medial and lateral malleolar zones, styloid process of the 5th metatarsal, and navicular[20]; (iv) positive anterior drawer or talar tilt dimple test suggesting ligamentous laxity [21-23]; (v) volume of the affected limb greater than 10% of the unaffected limb per water displacement volumetry[24]; (vi) previous history of ligament or bony reconstructive surgery to the ankle and foot; (vii) concomitant injury to other lower extremity joints; and (viii) medical conditions that serve as contraindications to mobilization/manipulation and transcranial magnetic stimulation, such as presence of pacemaker, metal in head, pregnancy, neurological disorders, recent use of stimulants or medications known to lower seizure threshold, and personal or family history of seizures.[25,26]

A total of 27 subjects will be recruited for this study (n = 9 per group). This sample size will provide >80% statistical power to detect differences in lateral star balance excursion performance based on an effect size d = 1.47 from Hale and colleagues[27] involving change in SBET score due to an exercise-based rehabilitation program in individuals with ankle sprains. Therefore, this study was powered to detect between-group differences in the selected lower extremity functional behavior following talocrural manipulation, which is thought to be the dependent variable in this study that will demonstrate the greatest intersubject variability.

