### Procedure

All subjects who meet the inclusion and exclusion criteria will be eligible for participation (Figure 1). Potential subjects also will be screened prior to enrollment into this study to determine presence of decreased ankle dorsiflexion range of motion (ROM) greater than 2 standard deviations from published norms for standard procedures for range of motion.[19] Upon arrival on the day of testing, participants will complete a 15-minute intake interview that includes questions about their medical and psychiatric history, and their current use of alcohol, nicotine and prescription or non-prescription drugs. The purpose of the interview is to obtain more detailed information about any factors that may influence either their eligibility to participate in the TMS/EMG procedures or the results of the TMS/EMG measurements themselves. Patients will then receive pre-intervention testing, randomization into intervention groups and study-related intervention, and post-intervention testing. Study procedures will last up to 3 hours. The Institutional Review Board of the University of Southern California (Los Angeles, CA, USA) approved the study protocol.

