#### Lower extremity functional behavior measurement

Following the ankle ROM tests, all subjects will receive a measurement of lower extremity functional behavior involving a star balance excursion test (SBET) conducted on a single limb. The SBET is a clinical test of dynamic balance.[32] Subjects will assume unilateral stance in the center of a grid marked circumferentially in 45-degree increments. After a learning trial consisting of 6 repetitions in each of the 8 test directions[33], subjects will complete 3 repetitions of single limb squat reach. Two trials will be completed: 1 trial each with the subject standing on the affected and unaffected limbs. Test directions include anterior, lateral, anterolateral, posterolateral, posterior, medial, anteromedial, and posteromedial. The evaluating therapist will record the distance achieved between the stance toe and the contacting portion of the reaching extremity for 3 repetitions in each direction. Fifteen seconds of rest will be provided between trials. Repetitions will be excluded if the subject (1) is unable to maintain weightbearing during the trial; (2) lifts the stance foot; (3) loses balance; or (4) does not maintain the hold or start positions for 1 second. This test demonstrates good reliability (ICC = .67–.97), and demonstrates discriminative validity between non-disabled individuals and patients with chronic ankle instability.[32,34]

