#### Functional behavior and ROM measurements

SBET measurements will be indexed to lower limb length as measured from anterior superior iliac spine to medial malleolus prior to data analysis. Two-sample t-tests with appropriate correction will be used to determine the statistical significance of differences in pre- and post-intervention ankle DF ROM, SEBT performance, and MEP/CSP data. Test-retest reliability and minimum detectable change will be determined for the 2 baseline measurements of MEP/CSP data.[37,38] Pearson correlations with appropriate statistical correction will be used to test the significance of associations among ankle DF ROM, SBET measurement, and TMS/EMG variables within subjects.

For all TMS, ROM, and lower extremity functional behaviour variables, two-factor multivariate analysis of variance with repeated measures for time will be used to determine the effects of repeated baseline testing and the intervention under study on SBET performance and ankle ROM measurements. Significant main effects will be reported if there are no significant interactions. If significant interactions are found, then one-way analysis of variance will be completed for each variable. Post-hoc testing will be performed as necessary with appropriate correction to determine the significance of pairwise comparisons. Pearson correlations with appropriate statistical correction will be used to test the significance of associations among ankle DF ROM, SBET measurement, and TMS/EMG variables within subjects.

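### The stated power of over 80% is for lateral SBET reach only, and the analysis section does not say which direction or limb is tested

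*Protocol article*

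**What the plan says.** The Subjects section of the Protocol article sets the sample size: "A total of 27 subjects will be recruited for this study (n = 9 per group"). It continues, "This sample size will provide >80% statistical power", and attaches that power to the ability to "detect differences in lateral star balance excursion performance based on an effect size d = 1.47". It concludes that "this study was powered to detect between-group differences in the selected lower extremity functional behavior following talocrural manipulation". No limb, significance level or sidedness is given with the statement.

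The section on lower extremity functional behavior measurement describes a wider data set. "Test directions include anterior, lateral, anterolateral, posterolateral, posterior, medial, anteromedial, and posteromedial", and "Two trials will be completed: 1 trial each with the subject standing on the affected and unaffected limbs".

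The Data Analysis subsection on functional behavior and ROM measurements indexes SBET measurements to limb length. It then plans two-sample t-tests with a correction it does not name. It also plans a two-factor repeated-measures multivariate analysis of variance covering all TMS, ROM and functional variables, to assess "effects of repeated baseline testing and the intervention under study on SBET performance and ankle ROM measurements". A significant interaction leads to a one-way analysis of variance for each variable, then to corrected pairwise tests. The subsection names no SBET direction, limb or composite.

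**The concern.** The sample size rests on one direction, one effect size and, implicitly, one test. Each assessment produces 8 × 2 = 16 direction-limb results, and the analysis section does not say which of them is the functional result. Outside the sample-size sentence, the lateral direction appears only as one item in the list of eight.

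This is the only endpoint with a stated power, and the third aim relates changes in corticospinal excitability to changes in function. If the analysis is followed across the SBET variables, there are two risks. A correction spread over directions and limbs uses up significance level that the power statement assumed was available to lateral reach, so an effect of the planned size could be missed. Without a named result, the choice of which reach supports a functional claim stays open until the data are seen. Both risks exist for a single two-arm contrast, so the issue is separate from how many pairs of arms are compared.

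**Working it through.** **Inputs.** From the Subjects section: n = 9 per group and d = 1.47 for lateral reach. From the measurement section: 8 directions and 2 limbs. Assumed: two-sided 0.05, because no level is stated, and no dropout, because testing is a single session ("Study procedures will last up to 3 hours").

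**1. The plan's own figure.** For a two-sample t-test, the degrees of freedom are 2 × 9 − 2 = 16 and the noncentrality is d × √(n/2) = 1.47 × √4.5 = 3.118. The critical value at two-sided 0.05 is 2.120. Noncentral-t power is **83.3%** (normal approximation 87.7%; one-sided t 90.9%). The claim of more than 80% is reproduced for one uncorrected comparison of one reach measure between two groups.

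**2. If the correction is spread over SBET results.** Bonferroni is used only as an illustration. Noncentrality stays at 3.118.

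| Results tested | Level per test | Critical t | Power at n = 9 | n per group for 80% |
|---|---|---|---|---|
| 1 | 0.05 | 2.120 | 83.3% | 9 |
| 8 (directions) | 0.05/8 = 0.00625 | 3.146 | 50.9% | 14 |
| 16 (directions × limbs) | 0.05/16 = 0.003125 | 3.475 | 40.0% | 16 |

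The normal approximation gives 65.0% for 8 and 56.5% for 16, so the drop does not depend on the method.

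**3. Three-group omnibus test.** With two groups equal and the third differing by 1.47, one-way analysis of variance has power 86.6% for one variable, 58.0% at 0.05/8 and 47.7% at 0.05/16. Using the F-test instead of a pairwise test does not remove the dependence on how many SBET variables are tested.

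**4. If the eight directions are averaged.** Let the other seven directions carry a fraction f of the lateral effect, with common correlation ρ. The composite effect size is

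1.47 × (1 + 7f)/8 ÷ √((1 + 7ρ)/8).

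The article gives neither f nor ρ. Power at n = 9, two-sided 0.05, is:

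| f | ρ = 0.9 | ρ = 0.5 |
|---|---|---|
| 0.25 | 18% | 27% |
| 0.50 | 41% | 59% |
| 0.75 | 67% | 86% |
| 1.00 | 87% | 97% |

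The range of 18% to 97% shows that no power figure for a composite follows from the article. Averaging could lower or raise the power.

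**The case against.** The strongest reply is that the passages are compatible. The Subjects section speaks of the selected functional behavior, which may mean that lateral reach is the variable to be tested. Eight directions on two limbs is the measurement scheme, and the analysis section does not say that all of them are tested. This is also a condensed article, and a fuller protocol or analysis plan may name the variable. This reply stands as far as it goes: if lateral reach on one limb is the only SBET result tested, the power holds. It does not dispose of the point. The article commits the sample size to one direction and then describes the analysis in some detail, for all functional variables and variable by variable, without carrying that direction forward. No section selects a limb.

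A reader might infer three stronger claims that the article does not support.

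- **That the stated power is wrong or cannot apply.** It reproduces, and it applies under the single-variable reading.
- **That the plan runs many uncorrected tests.** For independent tests the chance of at least one false positive would be 1 − 0.95⁸ = 34% over 8 and 1 − 0.95¹⁶ = 56% over 16, and less for correlated directions. But the t-tests and post-hoc tests are planned with correction, and the per-variable analyses of variance follow only a significant interaction. Those rates ignore both safeguards.
- **That averaging directions dilutes the effect.** This depends on an assumed smaller effect in the other directions, which the article does not give.

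It is also fair to object that Bonferroni is not the article's method, and that nothing makes the unaffected-limb reaches equal-ranking efficacy tests. The 51% and 40% are therefore illustrations, not estimates of the trial's actual power.

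**Conclusion.** The concern holds in a limited form. The stated power is secured only for one uncorrected two-group comparison of lateral reach (83.3%, two-sided 0.05 assumed). The analysis section leaves the tested SBET variable undefined, so that power is not established for the SBET analysis as written. The possible loss is material: under the illustrative Bonferroni correction, power falls to about 51% for 8 directions or 40% for 16 direction-limb results. A less conservative correction would lose less. This is a mismatch between the sample-size basis and the analysis that should be closed before data are examined. It is not an error in the power arithmetic.

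**What to change.** In the Data Analysis subsection on functional behavior and ROM, name change in limb-length-indexed lateral reach, standing on the affected limb, as the single functional endpoint matching the sample-size statement. State that it is tested without correction for direction or limb. Make the other seven directions and all unaffected-limb reaches secondary, either corrected as a family or reported with confidence intervals.

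If the sponsor prefers to test several directions or a composite, the Subjects section should restate the power for that analysis under the correction actually chosen. For a composite, it should also give the assumed effect and correlation.

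The first option costs about one sentence and needs no extra subjects or data. The small downside is that an effect confined to other directions could be reported only as secondary.

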### Research Design

Subjects each begin with pre-intervention TMS measures (motor thresholds and input-output curves), ankle range of motion (ROM) tests, and lower extremity functional behavior tests. Each pre-intervention measurement will be taken a total of 2 times with a 30 minute rest break between measurements. Subjects will then be randomized into 1 of 3 comparison groups, each to receive a different manual therapy intervention. Immediately following the intervention, subjects will receive post-intervention TMS measures, ankle ROM tests, and lower extremity functional behavior tests, identical to the pre-intervention assessments.

### Procedure

All subjects who meet the inclusion and exclusion criteria will be eligible for participation (Figure 1). Potential subjects also will be screened prior to enrollment into this study to determine presence of decreased ankle dorsiflexion range of motion (ROM) greater than 2 standard deviations from published norms for standard procedures for range of motion.[19] Upon arrival on the day of testing, participants will complete a 15-minute intake interview that includes questions about their medical and psychiatric history, and their current use of alcohol, nicotine and prescription or non-prescription drugs. The purpose of the interview is to obtain more detailed information about any factors that may influence either their eligibility to participate in the TMS/EMG procedures or the results of the TMS/EMG measurements themselves. Patients will then receive pre-intervention testing, randomization into intervention groups and study-related intervention, and post-intervention testing. Study procedures will last up to 3 hours. The Institutional Review Board of the University of Southern California (Los Angeles, CA, USA) approved the study protocol.

**Figure 1 F1:**
[figure not shown]
**Flow diagram for subjects' screening, testing, and intervention**.

### Pre-intervention testing

After informed consent is obtained, subjects will receive pre-intervention testing. Pre-intervention testing will include:

